## Abstract

**Introduction:**

The aim of the STOPPIT-3 study is to determine the clinical and cost effectiveness of antenatal corticosteroids (ACS) prior to planned birth of twins in a multicentre placebo-controlled trial with internal pilot.

**Methods and analysis:**

This study will comprise a multicentre, double-blinded, randomised, placebo-controlled trial in at least 50 UK obstetric units. The target population is 1552 women with a twin pregnancy and a planned birth between 35 and 38+6 weeks’ gestation recruited from antenatal clinics. Women will be randomised to Dexamethasone Phosphate (24 mg) or saline administered via two intramuscular injections 24 hours apart, 24–120 hours prior to scheduled birth.

**Outcomes:**

The primary outcome is need for respiratory support within 72 hours of birth. Secondary and safety outcomes will be included. Cognitive and language development at age 2 years will be assessed in a subset of participants using the Parent report of Children’s Abilities-Revised questionnaire. We will also determine the cost effectiveness of the treatment with ACS compared with placebo.

**Ethics and dissemination:**

STOPPIT-3 has been funded and approved by the National Institute of Healthcare Research. It has been approved by the West Midlands Research Ethics Committee (22/WM/0018). The results will be disseminated via publication in peer-reviewed journals and conference presentation and will also be communicated to the public via links with charity partners and social media.

**Trial registration number:**

ISRCTN59959611.

STRENGTHS AND LIMITATIONS OF THIS STUDYDouble-blind randomised multicentre trial.Cost effectiveness of antenatal corticosteroids use in twin pregnancy.Large sample size.Internal pilot to assess recruitment rate and intracluster correlation coefficient.Long term follow-up only possible in a subset of participants within the timeframe of the trial.

## Introduction

The overall aim of STOPPIT-3 is to address the uncertainty regarding the effectiveness of antenatal corticosteroids (ACS) prior to a planned birth of twins in the late preterm and early term period. ACS are widely administered via intramuscular (IM) injection to women at risk of preterm birth (defined as birth less than 37 completed weeks gestation) to reduce morbidity and mortality in babies born too early^1^ and have been recommended since the 1990s. ACS are known to be most effective if birth occurs 24–48 hours following administration of the first dose, with little or no benefit seen if birth is 7 days or more after administration.^1^

Twin pregnancy is common and associated with adverse outcomes for the babies, accounting for ~3% of live births but ~15%–20% of all neonatal care admissions.^2^ 2019 NICE guidance for twin pregnancy recommends planned birth at 37+0 weeks gestation in uncomplicated dichorionic (DC) twins (twins that have separate placentae), and planned birth at 36+0 weeks gestation in uncomplicated monochorionic (MC) twins (twins that share a placenta (~20% of twins)).^3^ Planned birth is by induction of labour (IOL) or caesarean section (CS). These slightly earlier, non-spontaneous births are at increased risk of respiratory morbidity and needing respiratory support requiring neonatal care admission.

There is, however, currently little evidence that ACS are as effective in twins, and similarly little evidence that ACS are effective in the late preterm and early term period which is the period that NICE recommend that twins are born.^3^ Evidence as to whether women having planned birth of twins should receive ACS is both conflicting and confusing, with practice known to be highly variable across the UK in this area. ACS are widely given to women with twin pregnancies having planned birth, despite recognition that ACS *may* have adverse effects on growth and neurodevelopment.^4 5^ There is some evidence that ACS in singleton pregnancies in the late preterm period (34+0–36+6 weeks) and/or prior to planned CS at term (37+0–38+6 weeks gestation)^6^ may have short-term benefits reducing respiratory morbidity and neonatal care admission. This evidence is often extrapolated to twin pregnancy, however, there is almost no evidence showing benefits of ACS from women with twin pregnancies. Differences in the pharmacokinetics of ACS,^7^ and mechanisms of fetal maturation (which may be accelerated in twins),^8^ may mean that ACS have different effectiveness at late preterm and early term gestations.

ACS are not devoid of harm. A large RCT of ACS in late preterm singletons demonstrated an increase in neonatal hypoglycaemia in the ACS group compared with placebo (number needed to harm 11).^9^ ACS have well-recognised detrimental effects on fetal growth (birth weight, length and head circumference) and conflicting results on neurodevelopment. Three studies (one RCT follow-up and two longitudinal studies) have shown detrimental effects on neurodevelopment following ACS exposure,^4 5 10^ but a recently published prospective follow-up study of the above RCTs of ACS in late preterm singletons demonstrated no adverse effect of ACS on childhood neurodevelopment outcomes.^11^ The balance of risk and benefit needs to be determined for twin pregnancies. Reducing term (>37 weeks gestation) neonatal care admission is a UK national priority. It poses a high cost to the NHS and separation of mothers and babies is detrimental to maternal well-being, mother–infant bonding and breastfeeding.^12^ There is evidence that ACS reduce serious respiratory morbidity and neonatal unit admission but there is potential for short (eg, hypoglycaemia) and long-term harms (eg, neurodevelopment). Either currently a substantial number of babies miss a morbidity sparing treatment; or a substantial number receive a potentially harmful treatment unnecessarily as practice varies substantially across the UK. STOPPIT-3 will provide the evidence to address this uncertainty.

## Methods

### Design

STOPPIT-3 is a multicentre double-blind randomised placebo controlled trial to determine the clinical and cost effectiveness of ACS versus placebo in women with a viable twin pregnancy with planned birth between 35+0 and 38+6 weeks gestation. An internal pilot phase will take place to assess recruitment rates. A nested economics analysis will assess cost-effectiveness of ACS versus placebo. The primary objective is to test the hypothesis that ACS reduce neonatal morbidity including the need for respiratory support within 72 hours of birth. The secondary objectives are to determine the effect of ACS on severe respiratory morbidity, perinatal mortality, maternal outcomes including breastfeeding and infection and the cost-effectiveness of treatment with ACS compared with placebo. The effect of ACS compared with placebo on childhood cognitive and language development at the age of two will also be assessed in a subset of twins. The study opened for recruitment in August 2022 and recruitment will run until August 2025.

### Health technology being assessed

A single course of Dexamethasone Phosphate (24 mg) given in two divided doses by IM injection to the thigh or buttock by appropriately qualified clinical or research staff 24 hours apart (±4 hours). Two formulations of ACS, Dexamethasone and Betamethasone, are recommended in the UK. Dexamethasone has been chosen over Betamethasone as it does not need to be stored in a fridge, is cheaper and is more widely available worldwide.

### Population

The target population is women with a confirmed viable twin pregnancy and planned birth between 35+0 and 38+6 weeks gestation. Women who are booked for their delivery at one of the participating study sites and who appear to meet the study eligibility criteria will be invited to participate. Medical records of women pregnant with twins will be reviewed by the maternity care teams for individual recruitment potential into the trial. We anticipate that all eligible women expecting twins and attending for antenatal care in each of the sites will be invited to participate. Women who appear to fulfil the inclusion criteria for the trial will be approached by a member of maternity care team after confirmation of a viable twin pregnancy at an appropriate antenatal clinic or ultrasound visit, usually between 16 and 24 weeks gestation. Women will be provided with a written short trial summary at this time. Women will then be provided with a detailed patient information leaflet and consent form later in their pregnancy (between 32 and 36 weeks gestation, see online supplemental material). The timings outlined for giving women trial information should be followed if possible, however flexibility for approaching women is permitted and deviation from the timelines set out here will not be recorded as a protocol deviation. If the woman waives this opportunity for early information but still wishes to participate, consent may be taken after a shorter time interval. Where possible the reason for an eligible woman being excluded or declining participation will be recorded, for input into trial metrics as per the Consolidated Standards of Reporting Trials statement.^13^

10.1136/bmjopen-2023-078778.supp2Supplementary data

### Eligibility criteria

The following inclusion criteria will apply at the screening assessment (all must apply):

Aged 16 years or older and able to provide electronic or written consent.Viable twin pregnancy (MC or DC) with a planned birth* scheduled between 35+0 and 38+6 weeks gestation including women who have a planned birth due to logistic reasons (eg, availability of beds or staff), parental preference or other maternal or fetal indications.Gestation established by scan at≤16 weeks according to NICE guidelines and known chorionicity.≥24 hours* and<7 days until planned birth.*Birth must be planned to take place at 35 or more weeks gestation, after IOL or CS. At the point of randomisation, there must be ≥24 hours until the planned CS or IOL date to allow two doses of the study drug to be administered, at 24 hours (±4 hours) apart prior to the planned birth.

The following exclusion criteria will apply:

Unable to give informed consent.Known or suspected major congenital fetal anomaly at the time of inclusion (defined as any structural or chromosomal anomaly that would influence management at or around birth or in the immediate postnatal period. Suspected isolated minor anomalies with lesser medical, functional or cosmetic consequences; or isolated limb abnormalities such as talipes can be included).Diabetes (pre-existing or gestational)—corticosteroid use may significantly disrupt glycaemic control in women with diabetes, with potential to ‘unblind’ treatment allocation and pose risk to these women. The effect of corticosteroids prior to planned CS in women with diabetes will be examined in other studies.Receipt of ACS within the 7 days prior to randomisation.Sensitivity, contraindication or intolerance to any of the ACS or any of its excipients.Chorionicity or gestational age are unknown.Other serious pregnancy morbidities which indicate either birth before 35 weeks or urgent birth within 24 hours.

### Outcomes

#### Primary outcome

The primary outcome is need for respiratory support within 72 hours of birth. This outcome encompasses a range of levels of support consisting of one or more of the following: continuous positive airway pressure (CPAP); supplemental oxygen by high-flow nasal cannulae for at least two consecutive hours; need for supplemental oxygen by low flow nasal cannulae or incubator oxygen for at least four continuous hours; mechanical ventilation; extracorporeal membrane oxygenation (ECMO). Stillbirth or neonatal death within 72 hours of birth will be included as competing events.

#### Secondary outcomes

Severe respiratory morbidity within 72 hours after birth (defined as one or more of the following: CPAP or high-flow nasal cannula for at least 12 continuous hours; supplemental oxygen with a fraction of inspired oxygen of at least 0.30 for at least 24 continuous hours; mechanical ventilation; ECMO; stillbirth; neonatal death within 72 hours of birth).Any admission to neonatal care (ie, admission for any reason and for any duration).Neonatal care admission within 72 hours of birth for 48 hours or more or any neonatal care admission (within 28 days of birth) or those requiring surfactant treatment or nitric oxide therapy.Apgar score at 5 min.Umbilical arterial cord pH.Umbilical arterial cord base excess.Newborn hypoglycaemia diagnosed within 48 hours of birth (defined as blood glucose of less than 2.0 mmol per litre).Newborn neonatal jaundice (defined as those requiring treatment with phototherapy according to NICE threshold for gestation and postnatal age).Birth weight centile.Head circumference at birth.All cause early onset sepsis within 72 hours of birth (defined as culture positive (pure growth from blood or CSF of a known bacterial pathogen) or culture negative (acute onset of illness with three or more predefined clinical signs)).Extended perinatal mortality (stillbirth or neonatal death up to 28 days).Stillbirth (death in utero).Neonatal death (death within 28 days of birth).Exclusive breastmilk nutrition at discharge.Confirmed or suspected maternal postpartum infection during hospital admission (defined by a new prescription of antibiotics, confirmed systemic infection on culture or endometritis as defined by the US Centres for Disease Control and Prevention).Cost effectiveness of treatment with ACS compared with placebo.Childhood cognitive and language development at 2 years of age determined by the Parent Report of Children’s Abilities-Revised (PARCA-R) score^14^ (in the first 340 women recruited to the trial).

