### Statistical analysis and sample size

The statistical analysis will be according to the intention to treat principle (ie, all participants will remain in their allocated group for analysis). Statistical significance will be at the 5% level with corresponding 95% CI presented. Randomised groups will be described at baseline and follow-up using mean (SD), median (IQR) and counts (with percentages) as appropriate.

For the primary outcome (respiratory support within 72 hours of birth), the OR (and 95% CI) for the treatment effect of ACS will be estimated adjusting for mode of delivery, treatment centre (if appropriate) and chorionicity with logistic regression. To account for the clustering effect within twin pairs, a random-effects logistic regression model will be used by fitting pregnant woman as a random effect.

Continuous secondary outcomes will be analysed using linear regression, and binary categorical secondary outcomes will be analysed using logistic regression as per the primary outcome. Secondary outcomes with more than two categories will be analysed using multinomial logistic regression.

Subgroup analyses, for example by sex of twins, chorionicity and presence of maternal comorbidity (eg, hypertension) will be considered.

No interim analyses are planned other than re-estimation of the intraclass correlation (ICC, assumed to be 0.3) following the internal pilot. This will be done by estimating the 95% CI (without, and possibly with, adjustment for covariates) as per the event rate around the observed ICC at 200 women with complete data, and if this 95% CI does not contain 0.3 corrective action will be taken.

We plan to recruit 1552 women randomised at 1:1 to ACS or placebo prior to planned birth. We will have 90% power at the 5% significance level to detect a relative difference in the neonatal primary outcome of respiratory support within 72 hours of birth between the groups of 33% (absolute difference of 4%) assuming an event rate of 12% in the placebo group and an ICC of 0.3, assuming 1% of missing data for the primary outcome.

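### As worded, the 48-hour neonatal admission outcome is met by any admission within 28 days, so its threshold has no effect and it nearly repeats the separate any-admission outcome

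*Protocol article*

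**What the plan says.** The protocol article, under Secondary outcomes, lists two neonatal admission outcomes one after the other.

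- The first is "Any admission to neonatal care (ie, admission for any reason and for any duration"). It states no time window.
- The second reads "Neonatal care admission within 72 hours of birth for 48 hours or more or any neonatal care admission (within 28 days of birth"), and closes with the surfactant and nitric oxide condition: "or those requiring surfactant treatment or nitric oxide therapy".

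Under Statistical analysis and sample size, "binary categorical secondary outcomes will be analysed using logistic regression as per the primary outcome". Both admission outcomes are binary, so both go into the same type of model. No other section of the article defines either outcome differently.

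**The concern.** The second outcome is a chain of three alternatives joined by *or*, and the middle one carries no condition on duration or treatment. If it is coded as written, a baby admitted for a few hours of observation on day 1 is an event, just like a baby who stays two weeks.

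A 48-hour threshold and a surfactant or nitric oxide criterion have little purpose in an outcome that any admission satisfies, least of all when any admission is already listed separately. The presumable aim was to identify longer or more intensive neonatal care. That is an inference, because the article gives no rationale for the outcome.

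What is at stake is a distinct endpoint. The Patient and public involvement section says the trial addresses a parent priority that includes length of stay in the neonatal unit. This is the only listed clinical outcome that grades a neonatal admission by how long it lasts, and as worded it does not do so. There is also more than one way to repair the sentence. If the choice is left open until results are known, the outcome is no longer prespecified.

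**Working it through.** **The plan's own figure.** The only sample-size figure concerns the primary outcome. It is checked here only to show that it is separate from this point. Inputs, all from Statistical analysis and sample size: 12% v 8%, 5% significance (taken as two-sided), 90% power, ICC 0.3, 1% missing data.

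- Babies per arm before clustering: [1.960·√(2·0.10·0.90) + 1.282·√(0.12·0.88 + 0.08·0.92)]² / 0.04², which rounds up to 1181.
- Design effect for twins: 1 + (2 − 1)·0.3 = 1.3.
- Women: 1181 × 2 × 1.3 / 2 = 1535.3.
- Allowing for 1% missing: 1535.3 / 0.99 = 1550.8, against 1552 stated. The figure reproduces, and nothing below depends on it.

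**The definition.** Write the three alternatives as:

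- A: admission within 72 hours of birth, lasting 48 hours or more.
- B: any neonatal care admission within 28 days.
- C: surfactant or nitric oxide.

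The outcome as written is A or B or C. Because 72 hours falls inside 28 days, A implies B. Hence A or B or C = B or C, and A drops out.

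As A cannot occur without B, six combinations are possible (1 = yes or event, 0 = no or non-event). Reading (a) is A or (B and C), meaning that the treatment condition qualifies the 28-day admission. Reading (b) is A or C, meaning that the middle alternative is deleted.

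| Row | B | A | C | As written | Without the 48-hour alternative | Any admission | Reading (a) | Reading (b) |
|---|---|---|---|---|---|---|---|---|
| 1 | 0 | 0 | 0 | 0 | 0 | 0* | 0 | 0 |
| 2 | 0 | 0 | 1 | 1 | 1 | 0* | 0 | 1 |
| 3 | 1 | 0 | 0 | 1 | 1 | 1 | 0 | 0 |
| 4 | 1 | 0 | 1 | 1 | 1 | 1 | 1 | 1 |
| 5 | 1 | 1 | 0 | 1 | 1 | 1 | 1 | 1 |
| 6 | 1 | 1 | 1 | 1 | 1 | 1 | 1 | 1 |

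*Becomes 1 if the baby is first admitted after day 28, since that outcome has no stated window.

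Four results follow.

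1. The columns with and without the 48-hour alternative agree in all six rows. The threshold reclassifies no baby, and this is exact.
2. The outcome as written and the any-admission outcome can differ only in row 2 (surfactant or nitric oxide without an admission within 28 days) and in row 1 when the first admission comes after day 28.
3. Row 3, an admission within 28 days that meets neither the 48-hour criterion nor the treatment criterion, is an event as written. It is a non-event under either repair. These are the babies that the threshold would be expected to separate out.
4. Readings (a) and (b) differ only in row 2, provided that (b) puts no time limit on the treatment. If (b) tied the treatment to the first 72 hours, the two would also differ for a later admission, for example one on day 10 requiring nitric oxide.

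**The case against.** The strongest reply is that this is a slip in one sentence and not a flaw of design. The word *those* has no clear antecedent. If the clause was meant to qualify admissions within 28 days, as in reading (a), the threshold works and the outcome is distinct. The article is a condensed document, and the full protocol, case report form and analysis plan may word the outcome correctly. That stands as a limit on the consequences. It does not remove the point, because the article does not leave the definition to another document. It states one, and the stated one fails if followed.

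Four stronger readings are tempting, and the article does not support them.

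- **That the trial will report one result twice.** A reader might infer this, but it assumes literal coding of the sentence, which the article cannot show.
- **That the two outcomes are identical.** They are nearly so. The 28-day window and the surfactant or nitric oxide alternative leave small gaps, and the article nowhere says that every baby given those treatments is admitted.
- **That the trial loses every means of telling brief from substantial care.** Severe respiratory morbidity has its own duration thresholds, though for respiratory support only. The Health economic analysis section collects neonatal admission and resource use up to 28 days, though for costing. Neither replaces a 48-hour admission outcome, but nothing suggests that duration data would be lost.
- **That length of stay is a national priority.** The Introduction gives that status only to reducing term neonatal care admission, which the separate any-admission outcome serves. Length of stay appears only among the parent priorities.

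**Conclusion.** The point holds for the wording. As written, any admission within 28 days meets the outcome, and the 48-hour threshold changes the classification of zero babies. This rests only on the sentence and on 72 hours lying within 28 days.

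Near-duplication of the any-admission outcome rests on one further assumption: that treatment with surfactant or nitric oxide without admission within 28 days, and first admission after day 28, are both rare. The article gives no figures for either. The purpose of the outcome is inferred, and the article does not show which repair was intended.

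One of 18 listed secondary outcomes is affected. The primary outcome, the sample size and the main comparison are untouched. It should be fixed, but it does not threaten the trial's main conclusion.

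**What to change.** Before unblinding, the sponsor should confirm the intended definition and restate it so that the unrestricted admission alternative no longer stands alone. Two repairs fit the existing words:

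- (a) Replace *or those requiring* with *requiring*. The outcome becomes admission within 72 hours for 48 hours or more, or any admission within 28 days requiring surfactant or nitric oxide.
- (b) Delete the alternative of any neonatal care admission within 28 days. The outcome becomes admission within 72 hours for 48 hours or more, or treatment with surfactant or nitric oxide. The 28-day limit goes with the deleted words, so the treatment criterion then needs a time window of its own.

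The choice belongs to the sponsor and should be made without sight of results by arm. The same correction should state the time window for the separate any-admission outcome. If the full protocol or analysis plan already has a workable definition, it is enough to bring the published wording into line with it.

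The cost is a sentence or two. The components (admission, its timing and duration, surfactant, nitric oxide) are already named in the definition, so no new type of outcome data is called for.

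### A new antibiotic prescription alone counts as maternal postpartum infection, so preventive courses started after birth are scored as infection and can dilute a safety comparison

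*Protocol article*

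**What the plan says.** In the protocol article, Secondary outcomes, the outcome is named "Confirmed or suspected maternal postpartum infection during hospital admission" and is then "defined by a new prescription of antibiotics, confirmed systemic infection on culture or endometritis as defined by the US Centres for Disease Control and Prevention". The three criteria are joined by or. The antibiotic criterion carries no indication, no minimum duration and no exclusion of prophylaxis.

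The same list is stricter elsewhere. Early-onset newborn sepsis without a positive culture must be "culture negative (acute onset of illness with three or more predefined clinical signs", and newborn jaundice counts only if phototherapy is required by a named threshold.

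The Design section puts "maternal outcomes including breastfeeding and infection" among the secondary objectives. According to the Introduction and the eligibility criteria, every participant has a birth planned by induction or caesarean section. The article gives no caesarean share, no rate of antibiotic use and no expected rate of maternal infection.

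**The concern.** The article states a case definition, and that definition admits women who are not cases. Site staff extract birth data from the medical notes, in at least 50 units. Someone who finds a new antibiotic entry after birth, given preventively to a woman with no sign of infection, must record an infection if they follow the definition literally. Another extractor may look to the outcome's name and leave her out. The definition does not settle which of them is right.

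At stake is a maternal safety comparison. If preventive prescribing is unrelated to allocation, the misclassification adds events to both arms and moves the ratio towards 1. For an efficacy outcome that error is conservative. For a harm it is not, since it makes a real excess of infection on corticosteroids harder to see.

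**Working it through.** **1. The plan's own figure.** The sample size rests on the primary outcome only: "We will have 90% power at the 5% significance level to detect a relative difference in the neonatal primary outcome", "assuming an event rate of 12% in the placebo group and an ICC of 0.3, assuming 1% of missing data for the primary outcome", with 12% v 8%. The pooled-variance formula without continuity correction is

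n = [1.960 × √(2 × 0.10 × 0.90) + 1.282 × √(0.12 × 0.88 + 0.08 × 0.92)]² / 0.04², which rounds up to 1181 babies per arm.

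With design effect 1 + (2 − 1) × 0.3 = 1.3, two babies per woman and 1% missing, the total is 2 × 1181 × 1.3 / 2 / 0.99 = 1551 women, against 1552 stated. The sample size reproduces and is not in question. The article states no power for maternal infection.

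**2. Inputs for the illustration.**
- From the article: "We plan to recruit 1552 women randomised at 1:1 to ACS or placebo prior to planned birth", hence 1552 / 2 = 776 women per arm, and the 5% significance level (taken as two-sided). There is one record per woman, so the twin design effect does not apply.
- Assumed: the true infection rate in each arm, and q, the share of uninfected women who meet the outcome only through a preventive prescription. q is taken as equal in both arms, which blinding makes reasonable.

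**3. Formulas.**
- Observed rate = p + (1 − p) × q.
- Observed difference = true difference × (1 − q).
- Power = Φ[(d − 1.960 × SE₀) / SE₁], where SE₀ is the pooled and SE₁ the unpooled standard error of the difference d. This is an unadjusted approximation to the planned logistic regression.

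**4. One case in full: true 10% v 15%, q = 10%.**
- Placebo: 0.10 + 0.90 × 0.10 = 0.190.
- Corticosteroid: 0.15 + 0.85 × 0.10 = 0.235.
- Risk ratio 0.235 / 0.190 = 1.24; difference 0.045.
- SE₀ = √(2 × 0.2125 × 0.7875 / 776) = 0.02077.
- SE₁ = √[(0.190 × 0.810 + 0.235 × 0.765) / 776] = 0.02074.
- Power = Φ[(0.045 − 0.0407) / 0.02074] = Φ(0.21) = 58%.

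**5. Results with 776 per arm.**

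| q | True 10% v 15%: observed | Risk ratio | Power | True 8% v 12%: risk ratio | Power |
|---|---|---|---|---|---|
| 0 | 10.0% v 15.0% | 1.50 | 85% | 1.50 | 75% |
| 5% | 14.5% v 19.3% | 1.33 | 71% | 1.30 | 57% |
| 10% | 19.0% v 23.5% | 1.24 | 58% | 1.21 | 44% |
| 20% | 28.0% v 32.0% | 1.14 | 40% | 1.12 | 29% |

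Allowing 1% missing (776 × 0.99 = 768 per arm) changes the 10% v 15% powers only to 84%, 70%, 58% and 40%.

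**6. Other base rates.** For a true 5% v 7.5%, power is only 53% at q = 0, and 23% at q = 10%. For a true 5% v 10%, it is 96% at q = 0 and 66% at q = 10%.

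**The case against.** The strongest answer is that the criterion should be read with the outcome's name. *Infection*, *postpartum* and *new* all narrow it, and a new prescription is most naturally the marker for the *suspected* part. That is a fair account of what was probably meant. It does not settle the matter, because the bracket states what defines the outcome and gives no indication for the prescription.

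The narrowing words do rule out a stronger reading. A reader might infer that all prophylaxis around caesarean section or induction is counted. Antibiotics given before or during birth are not plainly postpartum, so the text does not support that. The point concerns preventive courses started after birth.

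A reader might also infer that such courses are common, differ between units and overwhelm any harm signal. The article says nothing about prophylactic antibiotics. If sites record only treatment courses, q is near zero and nothing is lost. At low infection rates the comparison is weak even with a perfect definition, as 5% v 7.5% shows. On the absolute scale the dilution is also milder: at q = 10% the difference falls only from 5.0 to 4.5 percentage points.

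Nor does the article show that this is the only place where maternal harm is captured. It also refers to safety outcomes, adverse events and an independent data monitoring committee.

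Finally, this is a condensed article, and the full protocol or eCRF may already restrict the indication. That objection stands as a limit on the finding. The definition as published still needs to agree with whatever the sites use.

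**Conclusion.** The concern holds in a limited form. As published, a new antibiotic prescription is sufficient by itself, so a preventive course started after birth counts as infection. With blinding, and with preventive prescribing unrelated to allocation, the error dilutes the risk ratio and cannot be expected to create a false difference.

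The direction is clear; the size is not. In the 10% v 15% scenario, a q of only 5% costs about 14 percentage points of power (85% to 71%), and in the 8% v 12% scenario about 18 (75% to 57%). The loss therefore need not depend on heavy prophylactic use. These figures rest on assumed infection rates and an assumed q, and the loss is nil at q = 0. The documents do not support saying that the harm signal will be lost. The primary outcome and the sample size are unaffected.

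**What to change.** Reword the criterion as a new prescription of antibiotics, started after birth, to treat suspected or confirmed infection, excluding prophylaxis. Record the indication on the eCRF, judged by site staff while blinded. Report culture-confirmed infection and endometritis as separate components beside the composite, so that readers can see how far it is driven by prescriptions alone. If the full protocol or eCRF guidance already limits the indication, it is enough to confirm this and align the article's wording with it.

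The cost is one phrase and one eCRF field. For women already recruited, the indication could be sought in the medical notes that sites already use for data extraction. The small downside is that sites must judge the indication, and some entries will be unclear. Because that judgement is blinded, the remaining error should again be the same in both arms.
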